## 6.6. Follow-up of subjects withdrawn from treatment

Patients withdrawing from the study will be asked permission for the researchers to look into the available (para)medical data.

# 7. SAFETY REPORTING

## 7.1. Section 10 WMO event

Conform section 10, sub 1, of the WMO, the researcher will inform participants as well as the accredited ethical committee (METC) about an event that suggests that participation in the study has significantly larger disadvantages than expected in the study protocol. The study will be postponed during further evaluation by the accredited ethical committee (METC), unless delay would endanger the health condition of the participants. The researcher will take care of keeping all participants informed.

## 7.2. Adverse and serious adverse events

The assessments are not expected to result in adverse or serious adverse events.

## 7.3. Follow-up of adverse events

None

# 8. STATISTICAL ANALYSIS

Alpha=0.05 will be applied for all statistical testing.

## 8.1. Descriptives

Data will be described quantitatively; averages and standard deviations. Besides quantitative scores (where possible) on the questionnaires on awareness, life events, motivation, expectations/evaluation of training and open-ended questions on the impairments due to the hemianopia, the results of these questionnaires can also be described qualitatively.

## 8.2. Univariate analysis

*Primaire onderzoeksparameter*

The effect of training on the fixation and saccade parameters on the Dot Counting Task are analyzed in two ways:

1. A between-group analysis by comparing data from T2 of the training group with data from T2 of the control group, possibly corrected for data from T1.
2. A within-group analysis by comparing change between T1 and T2 with change between T2 and T3 in the control group using repeated measures analysis.

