**Primary outcome measures:** Eye movement parameters on scanning tasks (such as fixations, saccades, fixation duration, size of saccades, etc.). See *chapter 2: Objectives and research questions* for more information.

Possible risk: The effect measures do not include invasive testing. The effect measures have no adverse consequences for the participant, nor for his/her treatment at Royal Dutch Visio and there are no risks involved. Therefore, the burden is unassuming. When patients agree to participate in the study, the only thing they need to do is come to Groningen for the effect measurements on two or three separate days. Expenses for traveling and accommodation will be compensated. Patients know they can refuse or end participation in the study at any time, without any effect on their individual treatment at Royal Dutch Visio.

Additional information:

- The study is performed by Royal Dutch Visio in collaboration with the faculty GMW of the University of Groningen. Visio is responsible for implementing the training protocol and providing training. The faculty GMW is responsible for coordinating training and effect measurements.

- The interventions will be provided at several regional departments of Visio.

- The effect measurements will take place at the department of Neuropsychology of GMW located in the University Medical Center Groningen.

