# 2. OBJECTIVES AND RESEARCH QUESTIONS

Primary:

The aim of this study is to examine the effect of a compensatory scanning training (CST). The effects will be investigated on the level of functions, activities and participation.

The expectation related to the training is that patients learn to make larger and more efficient saccades towards the blind hemifield, shifting potentially interesting objects into the functional healthy part of the visual field, enlarging the visual field of search and decreasing search time. Herewith we strive to improve general mobility, increasing participation and quality of life.

The following research questions have been defined:

*1. Does CST result in larger, more frequent and faster saccades to the blind hemifield?*

*2. Does CST result in more accurate and faster detection of peripheral visual stimuli?*

*3. Does CST result in shorter search times in complex visual environments?*

*4. Does CST result in safer participation in slow traffic?*

*5. Does CST result in less bumping to objects in complex visual environments?*

*6. Does CST result in a decrease in self-reported visual disabilities?*

*7. Does CST result in increased self-reported mobility?*

*8. Does CST result in improved self-reported quality of life?*

The order of presentation reflects the build-up of possible causal relations regarding the possible effect of the intervention.

Secondary:

Furthermore, the predicting effects of several variables will be examined.

The following aspects will be examined:

1. Visual functions, of which size of the visual field defect is the most important
2. Awareness and understanding the HVFD and its consequences in daily life.
3. Motivation for training
4. Presence of important health changes and life events during and preceding the study.
5. Premorbid level of intelligence
6. Executive functioning
7. Memory

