## 4.4. Sample size

The sample size was based on previous studies on the effect of CST. There is no reason to expect negative effects of training. Therefore, calculation of sample size was based on one-sided testing. Section *6.1.1 Primary outcome measures* provides more information on the reasons for eye movement parameters as primary outcome parameters. The Effect Size (ES) is calculated based on previous studies on the effect of CST on the number of fixations and refixations [2,5]. Taking the lowest value encountered (ES = 0.65), a minimum of 30 participants per group is required (training group vs. control group; two independent groups; α = 0.05; β = 0.20; one-sided testing). When comparing pre and post assessments within the total group (n=60), an ES of 0.34 can be detected with power 0.80 and one-sided testing with 0.05 significance. This means that even in case of low effectiveness of compensatory scanning training, the group size is fully sufficient. We assume an inflow of 120 patients (n=120) and we take into account a loss of 30 patients (25%) based on medical history (remaining n=90), 15 patients (17%) after assessment of inclusion and exclusion criteria (remaining n=75), and 15 patients (20%) during the period of training and effect measurements (remaining n=60).

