# 6. METHODS

## 6.1. Study parameters

### 6.1.1. Primary outcome measures

Scanning strategy based on eye tracking (fixation and saccade parameters) on a Dot Counting Task (similar to the Dot Counting Task as used by Zihl, 1995 [2]).

The order of research questions as listed in chapter *2 Objectives and research questions*, reflects the build-up of possible causal relations regarding the possible effect of the intervention. The eye movement parameters are on the base of this build-up. After all, in case the intervention would lead to an improvement in self-reported mobility and quality of life, but not to an improvement on the eye movement parameters, it would be hard to argue that the improvement can be ascribed to specific aspects of the training. A non-specific effect of training cannot be ruled out completely in a study like this, even more so because the control group does not receive a placebo intervention. This is one of the considerations to take eye movement parameters as the primary outcome in the power calculation. A second reason was that the dependent variables in the previous studies (all within-subject repeated-measures designs) on the effect of CST mainly used these eye movement parameters on visual search tasks and not questionnaires on mobility and quality of life [3]. Although these outcome parameters are of larger clinical importance than eye movement parameters, they could not be taken as primary outcome in the power calculation, because the expected effect size could not be predicted based on the literature.

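### The primary outcome is an open set of eye-movement parameters, each with two unranked analyses at alpha 0.05 and no error control, so the primary claim has no defined error rate

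*Protocol*

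**What the plan says.** **What is primary.** Section 6.1.1 gives "Scanning strategy based on eye tracking (fixation and saccade parameters) on a Dot Counting Task". The Summary gives "Eye movement parameters on scanning tasks (such as fixations, saccades, fixation duration, size of saccades, etc", a list that is open at both ends and refers to scanning tasks in the plural. Section 6.1.2 lists four eye-tracked tasks, so the Summary can be read more widely than Section 6.1.1.

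**How it is tested.** Section 8.2 opens with "The effect of training on the fixation and saccade parameters on the Dot Counting Task are analyzed in two ways". The first way is "A between-group analysis by comparing data from T2 of the training group with data from T2 of the control group, possibly corrected for data from" (the quote stops just before the visit label, which is T1). The second is "A within-group analysis by comparing change between T1 and T2 with change between T2 and T3 in the control group using repeated measures analysis". Section 8.3 adds an optional multiple regression of Dot Counting Task performance in which group allocation is one predictor.

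**Error rate.** Section 8 says "Alpha=0.05 will be applied for all statistical testing". Section 8.3 refers to familywise error control under the secondary outcomes only.

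**Sample size.** Section 4.4 takes an effect size of 0.65, the lowest value from "previous studies on the effect of CST on the number of fixations and refixations". It derives 30 per group for two independent groups, one-sided, with alpha 0.05 and beta 0.20.

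**The concern.** A 5% error rate belongs to one defined hypothesis. Here the protocol defines neither which parameter carries the primary claim nor which of the two analyses decides it. Whether the between-group test is adjusted for T1 is also left open. The authors recognise multiplicity, since they address it for the secondary outcomes, but the primary outcome has no such protection.

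At stake is what a positive result would mean. Suppose one of several parameters reaches p<0.05 in one of the two analyses. Nothing in the protocol prevents that from being reported as the primary effect, and nothing tells a reader how many chances there were. The power statement is affected too, because it was computed for one test. Naming the primary endpoint and the deciding test is the protocol's task, so a separate analysis plan would not remove the point.

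**Working it through.** **1. Reproduce the sample size.** Inputs from Section 4.4: ES 0.65, one-sided alpha 0.05, power 0.80.

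n per group = 2(z₀.₉₅ + z₀.₈₀)² / ES² = 2(1.645 + 0.842)² / 0.4225 = 29.3, rounded up to 30. The t-based value is 29.97. The stated 30 per group is correct for one one-sided between-group test.

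**2. Bound for independent tests.** The chance of at least one false positive in m independent tests at 0.05 is 1 − 0.95^m.

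| Tests | Chance of at least one |
|---|---|
| 2 (one parameter, both analyses) | 9.8% |
| 4 (four parameters, one analysis) | 18.5% |
| 8 (four parameters, both analyses) | 33.7% |

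**3. Allow for correlation.** The tests are not independent. Parameters from one task are probably correlated, and the control group's T2 values enter both analyses. A simulation under no training effect and no practice effect used 30 per group and the two Section 8.2 tests per parameter. It was run one- and two-sided, with and without T1 adjustment.

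Assumptions, none of them in the protocol:
- four parameters, the number of examples in the Summary;
- a correlation of 0.6 between visits;
- a common correlation between parameters, varied from 0 to 0.9;
- success declared if any test is significant.

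| Correlation between parameters | Both analyses | Between-group only |
|---|---|---|
| 0 | 30-33% | about 19% |
| 0.3 | 27-30% | 17-18% |
| 0.5 | 23-28% | 14-16% |
| 0.7 | 20-24% | 12-13% |
| 0.9 | 14-17% | about 9% |

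Taking these with the independence bound, the ranges are about 14-34% for both analyses and about 9-19% for the between-group test alone. With a single parameter, running both analyses gives 9-10%. With six parameters and both analyses, the range is 16-46%.

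**4. Power if multiplicity were repaired afterwards.** With 30 per group and ES 0.65, power ≈ Φ(0.65·√(30/2) − z₁₋α) = Φ(2.517 − z₁₋α), one-sided. The last column applies the formula of step 1 with the adjusted alpha.

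| Confirmatory tests | Bonferroni alpha | Power | n per group for 80% |
|---|---|---|---|
| 1 | 0.05 | 81% | 30 |
| 2 | 0.025 | 71% | 38 |
| 4 | 0.0125 | 61% | 45 |
| 8 | 0.00625 | 51% | 53 |

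The t-based powers are slightly lower: 80% for one test, 59% for four and 48% for eight.

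**The case against.** **The between-group comparison clearly leads.** Section 4.4 sizes that comparison for 30 per group. Sections 3 and 6.2 describe it first and bring in the within-patient comparison as an addition. This stands in part. A reader might infer from Section 8.2 that the two analyses are co-equal throughout the protocol, but they are unranked only in that section. Since Section 8.2 is where the primary analysis is specified, the ranking should be written there. Counting only the between-group test still leaves about 9-19% for four parameters.

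**The protocol does not say that any hit is a success.** True. A reader might infer a fixed false-positive rate, for instance 25-40%, as a property of the plan. The documents do not support that: it needs an assumed number of parameters, moderate or low correlations, both analyses counted and an any-hit rule. The defect is that no rule excludes that use, so every figure here is conditional.

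**The endpoint definitions conflict less than they seem to.** A reader might count the sample-size parameters and research question 1 ("Does CST result in larger, more frequent and faster saccades to the blind hemifield") as further, competing primary endpoints. Section 4.4 only names the source of the effect size, and number of fixations falls within the class in Section 6.1.1. Research question 1 is a question and not an endpoint definition. The wording conflict that remains is scanning tasks in the Summary against the Dot Counting Task in Section 6.1.1.

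**One-sided testing is not settled.** Section 4.4 makes the calculation one-sided, and Section 8 does not state the sidedness of the tests. The ranges above therefore cover both.

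**Conclusion.** The point holds. The primary outcome is an open class, Section 8.2 gives each member two unranked analyses at 0.05, and only the secondary outcomes have error control. As written, the primary claim has no defined error rate.

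If any significant parameter may be claimed, the risk is well above 5%. With four parameters assumed, it is about 14-34% with both analyses and about 9-19% with the between-group test alone, depending on the assumed correlations. It rises if more parameters are tested. The mildest of these cases, four highly correlated parameters and one analysis, still nearly doubles the nominal rate.

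The sample size itself is correct, but its 80% power belongs to a single one-sided between-group test. The textual defect is certain. Its size rests on the assumptions listed in the working.

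**What to change.** Amend the protocol before any unblinded look:

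- **Parameter.** Name one Dot Counting Task parameter as primary, with its favourable direction and the sidedness of its test. The natural choice is whichever of number of fixations or number of refixations supplied the effect size of 0.65. Section 4.4 does not say which, so the sponsor should state and justify the choice.
- **Test.** Make the between-group comparison at T2 the only confirmatory test, and state T1 adjustment as fixed.
- **Second parameter, if kept primary.** Apply Holm across the two and restate the power. At a one-sided 0.025, the level of Holm's first step, 30 per group gives about 71% at ES 0.65.
- **Everything else.** Label the within-control analysis and all other eye-movement parameters supportive or secondary.
- **Alignment.** Bring the Summary, Section 6.1.1 and Section 8.2 into line with this choice.

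This is a change of wording. With one parameter and one one-sided test, the 30 per group and 80% power stand, and nothing changes for participants. The cost is that the other eye-movement parameters, including saccade measures named in research question 1 if one of the fixation counts is chosen, lose primary status.

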5. In case the patient is included and has given informed consent, the patient is randomly allocated to the training group or control group (method of minimization, see for more information section *6.2 Selection*). Allocation to one of the two groups will not affect the moment at which the training starts. At Royal Dutch Visio, a waiting list of several months preceding treatment is not unusual. Patients from both the training group and the control group will visit the University Medical Center Groningen for a pre-assessment (the week before onset of training at Royal Dutch Visio) and a post-assessment (after 10 weeks of training). The control group will participate in a third assessment, 10 weeks before the pre-assessment (the so-called -10 assessment). By looking at the results from the pre-assessment and post-assessments of the training group and the results from the -10 assessment and pre-assessment of the control group, the effect of 10 weeks of training is compared to the effect of 10 weeks on the waiting list. In addition, the effect of treatment on the individual level can be examined by comparing the results from the post-assessment to the results from the -10 assessment and pre-assessment in the control group (within-patient repeated measures design). Including the post-assessment in the control group also increases power of the study.

In order to provide compensatory scanning training close to the patients’ residence, training will be provided at several locations of Royal Dutch Visio throughout the Netherlands, including Haren, Leeuwarden, Apeldoorn, Rotterdam and Haarlem. The final training protocol is composed in Haren. Therapists working at the participating departments of Visio received additional education in providing the training conform protocol. The training and diagnostic assessments take place at the department of Visio where the patient has registered.

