## 8.3. Multivariate analysis

*Primary outcome measures*

Using multiple regression, a predicted model can be formulated, in which performance on the Dot Counting Task can be predicted from several variables, such as group allocation (training group vs. control group).

*Secondary outcome measures*

The effect of training on the questionnaires, scanning tests, mobility tests and the reading test will be examined using multivariate analysis (MANOVA or mixed design ANOVA), so we can control for familywise error rate.

In addition, the effect of training will be examined by comparing test performance in the control group with the preceding measurement using multivariate analysis (MANOVA for multiple repeated measures design: 1 group, 3 time points, several outcome parameters).

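### The second of two unranked analyses of the primary outcome confounds training with second versus first retest, and the claimed power gain from the control group's post-assessment needs an unstated assumption

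*Protocol*

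**What the plan says.** Protocol section 8.2 introduces the primary analysis with "The effect of training on the fixation and saccade parameters on the Dot Counting Task are analyzed in two ways". The first way is a randomised comparison, "comparing data from T2 of the training group with data from T2 of the control group, possibly corrected for data from T1". The second stays within one group, "comparing change between T1 and T2 with change between T2 and T3 in the control group using repeated measures analysis". Nothing says which one decides if they disagree.

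Section 3, repeated in section 6.2, fixes the order of visits. Both groups have a pre-assessment and a post-assessment around the training, and "The control group will participate in a third assessment, 10 weeks before the pre-assessment (the so-called -10 assessment"). So in the control group T1, T2 and T3 are read here as the -10, pre- and post-assessments. In the training group T1 and T2 are the pre- and post-assessments. The same two sections add: "Including the post-assessment in the control group also increases power of the study". No figure or condition is attached.

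Two other places rely on comparisons without a concurrent untrained group. Section 4.4 says "When comparing pre and post assessments within the total group (n=60), an ES of 0.34 can be detected" and takes this as showing that the sample is large enough even if training works only weakly. Section 8.3 plans, for the secondary outcomes, a "MANOVA for multiple repeated measures design: 1 group, 3 time points, several outcome parameters".

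The protocol mentions no practice or retest effect and no parallel task versions. It makes no assumption about how gains compare over the two control intervals.

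**The concern.** A patient counting dots under eye tracking for the second or third time may do better through familiarity alone. In the control group the first retest always falls in the untrained interval and the second always in the trained one. Order and training are therefore completely aliased, and the training group, which has no third visit, cannot separate them.

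Two things are at stake. First, a confounded contrast stands level with the randomised one for the primary outcome, in a protocol that presents randomisation as its advance over within-patient designs. If the two disagree, the document gives no rule. Second, the sample-size argument draws comfort from T3 and from the pooled pre-post comparison. For the training effect, that comfort depends on an assumption the protocol never states.

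**Working it through.** **The plan's own figures.** Inputs from section 4.4: effect size 0.65, one-sided alpha 0.05, power 0.80, two independent groups. n per group = 2(1.645 + 0.842)² / 0.65² = 29.3, so 30; this reproduces. For the pooled pre-post comparison with n = 60, the detectable effect is (1.645 + 0.842)/√60 = 0.321, so the stated 0.34 is slightly conservative. The arithmetic is sound; the question is what these comparisons estimate.

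**Assumptions.** The protocol gives neither the correlation r between assessments nor any retest gain. Both are assumed: r from 0.5 to 0.8, gains in SD units, unit SD at each visit, common T1 mean, 30 per group, compound symmetry unless stated.

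**Step 1: what the second analysis estimates.** Let τ be the training effect and g1, g2 the first and second retest gains.

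- Training group means: T1 = μ; T2 = μ + g1 + τ.
- Control group means: T1 = μ; T2 = μ + g1; T3 = μ + g1 + g2 + τ.
- Second analysis: (T3 − T2) − (T2 − T1) = τ + (g2 − g1).
- First analysis: training T2 − control T2 = τ. Both groups are at their first retest, so g1 cancels.

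| g1 | g2 | bias g2 − g1 | a true 0.65 appears as |
|---|---|---|---|
| 0.1 | 0.1 | 0 | 0.65 |
| 0.1 | 0 | −0.10 | 0.55 |
| 0.2 | 0.1 | −0.10 | 0.55 |
| 0.3 | 0.1 | −0.20 | 0.45 |
| 0.3 | 0 | −0.30 | 0.35 |

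The bias favours training only if the second gain exceeds the first. At g2 − g1 = +0.2, the one-sided type I error would be 0.156 (r = 0.5) or 0.204 (r = 0.7).

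**Step 2: precision.** The second analysis has variance 6(1 − r)/30. The T2 comparison adjusted for T1 has variance 2(1 − r²)/30. The ratio is 3/(1 + r), which exceeds 1.5 for any r below 1.

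| r | T1-adjusted T2 comparison | within-control contrast | ratio | power at 0.65, T2 vs within-control (equal gains) |
|---|---|---|---|---|
| 0.5 | 0.0500 | 0.1000 | 2.00 | 0.897 vs 0.659 |
| 0.7 | 0.0340 | 0.0600 | 1.76 | 0.970 vs 0.843 |

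Under first-order autoregressive correlation the gap narrows but does not close: standard errors are 0.224 vs 0.289 at r = 0.5, and 0.184 vs 0.214 at r = 0.7.

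**Step 3: does the control T3 add power for τ?** Generalised least squares on the means above; the variance of τ is the matching element of the inverse of Σ 30·X′V⁻¹X over the two groups.

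| Model for the second retest gain | r = 0.6, without T3 | r = 0.6, with T3 |
|---|---|---|
| g2 free | 0.0427 | 0.0427 |
| g2 = g1 | 0.0427 | 0.0414 |
| g2 = 0 (no further practice) | 0.0427 | 0.0225 |

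With g2 free, the T3 mean carries its own unknown parameter, so with complete data it says nothing about τ. Under equal gains, the condition that makes the second analysis unbiased, variance falls by (0.0427 − 0.0414)/0.0427, about 3%. The large gain needs no practice after the first retest, and then the second analysis is biased by −g1. Imposing g2 = 0 when both gains are really 0.2 SD biases that model's estimate by +0.133 (r = 0.5).

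**Step 4: the pooled n = 60 remark.** Pre-post change in all 60 estimates τ plus an average retest gain, with no untrained group to subtract. With τ = 0 and an average gain of 0.1 SD, the one-sided type I error is 0.19 (r = 0.5) to 0.26 (r = 0.7).

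**The case against.** **A hierarchy is implied.** Sections 3 and 6.2 give the randomised comparison first and bring in the within-patient one as an addition, for effects in individuals. The sample size rests on two independent groups, and section 8.2 lists the between-group analysis first. This has force: the fix mostly makes explicit what the authors may have intended. But section 8.2 does present both as analyses of the training effect on the primary parameters, and it ranks neither.

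**The likely error is conservative.** If practice gains shrink, the second analysis understates the effect. With a bias of −0.2 SD at r = 0.6, its one-sided false-positive rate is near 0.01. This stands. A reader might infer that the analysis manufactures benefit; nothing in the documents supports that, since it would need a larger second gain than first.

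**The power sentence may be true.** A reader might conclude that it is false for every unbiased analysis. That goes too far. If gains are truly equal, or truly stop after the first retest, a model saying so is unbiased and more precise with T3. T3 can also recover a trace of information when T2 is missing: with 20% of control T2 values missing (assumed), the standard error falls from 0.2372 to 0.2357 at r = 0.5. T3 further gives post-training data on all 60 patients for the secondary objective on predictors, and the sentence does not say which analysis it means. The fault is the missing condition.

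**The pooled test is not a primary analysis.** A reader might infer from section 4.4 that it is. It appears there only as a detectable-effect remark, and neither section 8.2 nor 8.3 names it, so its false-positive rates are no charge against section 8.2.

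**No self-contradiction.** The protocol objects that earlier work used only within-patient designs; adding one beside a randomised comparison is consistent with that.

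**Conclusion.** The concern holds in limited form. The within-control analysis estimates the training effect plus the difference between second and first retest gains, and no data in this trial separate the two. That follows from the visit schedule and needs no assumption. Its size does: 0 to −0.30 SD over the gains assumed here, zero if gains are equal, and in training's favour only if the second gain is larger. The protocol gives no retest gain or correlation, so these are ranges, not estimates. Under compound symmetry the analysis is also less precise than the T1-adjusted T2 comparison by the factor 3/(1 + r).

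For the training effect, the power sentence in sections 3 and 6.2 is conditional on an unstated assumption about the second retest gain. The benefit is nil with free visit effects and complete data, about 3% of variance under equal gains, and large only if practice stops after the first retest. The detectable effect of 0.34 in section 4.4 is correctly computed, even slightly conservative, but with no untrained comparator it does not show that the sample suffices to demonstrate a training effect. The randomised T2 comparison and its 30 per group are untouched.

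**What to change.** 1. Section 8.2: name the between-group T2 comparison, adjusted for T1, as the sole primary analysis, replacing the present optional adjustment.
2. Section 8.2: label the within-control comparison supportive, and state that it is unbiased only if the T1-to-T2 and T2-to-T3 retest gains are equal.
3. Section 8.3: give the one-group, three-time-point MANOVA of the secondary outcomes the same label and stated assumption.
4. Sections 3 and 6.2: qualify the power sentence. For the training effect, any gain depends on an assumption about the second retest gain. If the sentence was meant for the predictor analyses, say so.
5. Section 4.4: note that the pooled n = 60 figure has no untrained comparator, and do not use it to support the claim that the group size suffices to show a training effect.

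The cost is wording only. No visit, measurement or patient changes, and T3 is still collected and reported. The one small downside is a less favourable power statement.
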